### Brief Summary (English)

This national project is the first to include all SNAP factors (Smoking, Nutrition - both obesity & malnutrition - Alcohol, and Physical activity) in a combined intervention aiming at risk reduction for patients scheduled for ventral hernia repair. It will generate new knowledge of the effect on risk reduction via intensive lifestyle intervention 4 weeks prior to surgery.

The overall goal is to reduce the inequity in health via perioperative STRONG lifestyle intervention aiming at a better health gain by surgical risk reduction at short time and improved health on longer time. In total, 2x200 surgical patients disadvantaged by preoperative risky lifestyle will participate.

The primary outcome is postoperative complications. Other important outcomes are clinically relevant lifestyle improvements, frailty and comorbidity symptoms, patient motivation and reflections, health-related quality of life and cost-effectiveness on short and longer time. In addition, possible dose responses between lifestyle at surgery and complications, health & costs, and association between self-reported and validated lifestyles.

This project builds further on the ongoing and smaller STRONG-Cancer project for risk reduction at surgery with change in lifestyle as the primary outcome, approved in 2020 (H-20081571; P-2020-95).

Collaboration among:

4 Surgical Departments at:

HERLEV Hospital ([name]), HORSSENS

Regional Hospital ([name]), Zealand

University Hospital KØGE

([name]), and

Holbæk Hospital ([name])

and

The Danish Centre for Health

Economics at University of

Southern Denmark ([name])

and

The STRONG Team at WHO-

CC, Parker Institute at

Bispebjerg-FREDERIKSBERG

Hospital ([name])

## 2. Objectives

### 2a) Problem description, hypotheses, outcomes, and the rationale

Despite the great developments taking place during and after surgery, e.g., intraoperative techniques and enhanced recovery after surgery (the ERAS protocol), there is a large untapped potential for risk reduction in the preoperative period via effective lifestyle intervention targeting one or more co-existing risky lifestyles: Smoking, malNutrition, obesity, risky Alcohol intake and insufficient Physical activity (SNAP).

The STRONG project is national multicentre research with international impact. The overall goal is to obtain the potential extra health gain from the individually tailored, combined and intensive lifestyle intervention – STRONG - in relation to surgery, thereby adding to lower the inequity in health. As SNAP factors are frequent and have a negative social gradient, they strike hardest among disadvantaged patients, thereby developing most postoperative complications. In this project we would be able to reach out to surgical patients, who have not been reachable otherwise.

This clinical research benefits from mixed methods and comprehends several sub-studies:

1. Efficacy of the 6-week preoperative STRONG-program compared to treatment as usual (TAU) on (RCT):
  - A. risky lifestyles, preoperatively and complications, 1-month postoperatively
  - B. risky lifestyles and complications at 3 and 6-month follow-up
2. Efficacy of STRONG compared to TAU on health gain after 6 months and 2-year follow-up
3. Cost-effectiveness of the STRONG program on short and longer term (for 1. A+B and 2.)
4. Prevalence of SNAP factors in the potential study population and the potential for risk reduction.
5. Secondary analyses (Cohort analyses):
  - A. Dose-response of SNAP factor improvement (number/type) and complications as well as predictors for complication-free hernia repair
  - B. Dose-response of SNAP factor improvement (number/type) and health on long-term as well as predictors for improved health
  - C. Associations between self-reported and validated lifestyles
  - D. Associations between patient reflections of motivation, priority, self-efficacy, and lifestyle changes (Nested Qualitative analysis to the intervention group)

### The hypotheses

The primary hypothesis is that STRONG halves the postoperative complications within 1 month compared to the daily routines.

Secondly, improvement of postoperative complications after 3 and 6 months, risky SNAP lifestyles, health, and the cost-effectiveness as well as improvement of health and costs after 2 years.

In addition, we hypothesise associations

- between preoperative patient reflections and successful change of SNAP factors
- as a dose-response of SNAP factor improvement and complications, as well as predictors for complication-free hernia repair
- as a dose-response of SNAP factor improvement and health gain, as well as predictors for a health gain
- between self-reported and validated SNAP factors.

### The outcomes

The primary outcome is postoperative complications according to the Clavien-Dindo classification. Secondary outcomes are improvement of risky SNAP lifestyles (self-reported and validated), risk evaluation (according to the lifestyle categories in the ASA-score), patient reflections, health (measured by health-related quality of life, symptoms of frailty, and co-morbidity) and costs (measured as individual direct and indirect healthcare costs per patient based on perioperative costs, time back to work or reuptake of previous activities, total stay, and visits/contact to hospital and primary healthcare (from the national health registries).

### The rationale

The clinical STRONG project is based on the rationale

- that risky SNAP factors increase postoperative complications
- that preoperative intensive mono-factor intervention prevents a part of the complications
- that successful SNAP factor intervention improves health on longer term

In real life, several patients have co-existing risky lifestyles. Hitherto, no RCTs have integrated all SNAP factors. Therefore, time has come to take a common grab of the five SNAP factors as in the STRONG prehabilitation and establish new knowledge of the effect on postoperative complications, health & costs, and patient reflections.

### *2b) The background (Reference numbers refer to the list in chapter 16)*

Surgery remains the gold standard of treatment for many diseases including ventral herniation, but the outcomes are poor among patients with unhealthy lifestyles; thus, strategies to further optimise the perioperative care are increasingly important. The improved intraoperative techniques and enhanced recovery after surgery (ERAS), e.g., the ERAS protocol, are highly relevant – including for ventral hernia repair. However, there is a large untapped potential of risk reduction in the preoperative period, in particular the modifiable risk factors, which can be targeted with preventive strategies.

Systematic screening and related intervention for the SNAP factors prior to surgery are only fragmentally implemented in the surgical pathways. This is despite the World Health Organization (WHO) recommendations and the surgical guidelines endorsing all patients to be offered evidence-based support for risk reduction, as despite the American Society for Anesthesiologists (ASA) inclusion of relevant details on alcohol, smoking and obesity in the international preoperative risk evaluation for adults, the ASA-score.

The SNAP factors each adds independently to the surgical risk with about 50% for daily smoking, alcohol > 2 drinks/day, and severe malnutrition — similar to the risks related to severe cardiac, pulmonary, and kidney insufficiency. Obesity after both major and minor surgery and low physical activity are followed by a 10–20% increase in complication rates. Frailty is an example of co-existing SNAP factors with a major impact on the surgical outcome.

### Pathophysiological mechanisms

Patients with an unhealthy lifestyle develop the same type of complications as all other patients, just more frequently. The pathophysiology involves a comprehensive suppression of several organ systems of importance for surgical outcomes, such as low immune capacity, disturbed wound and tissue healing, cardiac and lung dysfunctions, and increased stress-response amongst others. These dysfunctions exist prior to surgery and add to the surgical trauma itself, often targeting the same organ functions. The increased postoperative complications are developed from the SNAP factors even without clinical diagnosis like alcohol-related liver disease and smoking-induced lung disease. The organ damage is often subclinical and takes place at the cellular level, thus reducing the extra capacity that usually supports the patient successfully during surgery and recovery.

### Need for a combined programme

The risk at surgery increases with co-existing risk factors, and thereby even minor surgery can lead to a bad outcome, but no published integrated program exists targeting all five SNAP factors except for the STRONG program^22.

We and other research groups have previously shown that an intensive intervention aiming at complete smoking or alcohol abstinence for 4 to 8 weeks halves the postoperative complication rate and indicates a sustained effect for longer time. For weight reducing programs, again the intensive intervention has a better effect on preoperative obesity than shorter programs.

Preoperative inspiratory exercise for 1–2 weeks reduces postoperative pneumonia, while malnutrition intervention before surgery is part of the international guidelines. Physical exercise improves respiratory fitness and functionality and followingly reduces postoperative recovery, but the impact on complications has been disappointing. However, a recent systematic review has identified a reduction of lung complications after major lung and cardiac surgery, but it is still inconclusive for other surgical interventions. The four randomised trials on frailty intervention (exercise and nutrition) show no effect on postoperative outcomes.

Smith and co-workers identified no randomised trials evaluating the efficacy of preoperative obesity intervention outside bariatric surgery. After their literature search period, one randomised trial has been published. Despite a significant preoperative weight reduction in the intervention group, the development of postoperative complications was similar in both groups.

Overall, there is a call for prehabilitation including more SNAP strategies, and the European Hernia Society strongly recommends conduction of high-quality studies of prehabilitation in relation to ventral hernia repair.

As the first worldwide, our research group tested a combined intensive smoking and alcohol cessation intervention, which was well received by the patients. The intervention took place shortly prior to the cancer surgery and thereby probably reduced the overall expected effect on postoperative complications (64% versus 70%), despite the high successful quit rates (51% versus 27%). Interestingly, the intervention group had lower number of patients with three or more complications on short and longer term^40.

We have also identified a minimal impact only of the social gradient on the effect of the national intensive smoking cessation intervention; thus, far from the social gradient among smokers - and that program is used in the STRONG project. In addition, the social inequality in health promotion success could be minimised through positive/selective involving procedures and support during the total intervention. A full SNAP intervention like the STRONG program is further supported by the results from secondary analyses that intensive mono-factor intervention on smoking and alcohol did not affect other risky lifestyles among surgical patients.

We are conducting a systematic review with a network meta-analysis on published randomised trials evaluating the effect of preoperative lifestyle intervention for two or more co-existing SNAP factors (PROSPERO: CRD42022282611). After screening the almost 18,000 eligible studies, the result of 19 trials is disappointing regarding the number of SNAP factors intervened. There is not published randomised trials aiming at all 5 SNAP factors but there is one study on smoking + alcohol cessation intervention from our group, one on smoking + respiratory training, and the rest on physical/respiratory training + any nutrition intervention. We experience a general lack of predefined inclusion criteria on nutritional level and physical activity. The risky SNAP factors are carefully predefined in the STRONG project.

### **Cost-effectiveness**

It is important to consider the costs of the STRONG in relation to the surgical outcomes. The cost-analyses are conducted via the national health registries including the individual DRG registry together with data collected in the project.

### **State of the art for Ventral hernia repair and SNAP factors**

Internationally and nationally, more and more scientific activities are performed aiming towards evidence-based guidelines, including uniform reporting of complications and patient reported outcomes as well as the use hereof. The Danish Hernia Database plays an important role in implementation and follow-up of these activities. It does, however, not include the SNAP factors, yet.

A major systematic review on ventral hernia repair has recently updated the evidence, including for the SNAP factors. Two randomised trials were identified for smoking, one Danish study by Sørensen and co-workers reporting no effect on wound complications after only low intensive interventions: Simple advice versus simple advice with reminding (4/48 = 8% and 6/101 = 6%). The other trial is Swedish by Lindström and co-workers. They reported any complication after ventral hernia repair which, however, constitutes a sub-group on 38 patients, 21 in the intervention group receiving intensive intervention and 17 in the control group receiving usual care, respectively. The total complication rate after hernia repair was halved after smoking cessation intervention; 6/21 in the intervention group versus 10/17 in the control group or 29% versus 59%. The complications were mainly wound complications (Authors personal information). No randomised trials were identified for preoperative obesity intervention outside bariatric surgery for nutrition or physical activity as mono-factor intervention. Alcohol intervention is not mentioned at all. Nevertheless, one trial used combined intervention aiming at both obesity and low fitness, followed by a 2-year follow-up (see next paragraph).

More than twenty years ago, the question of a higher impact of co-existing SNAP factors on the complication rate than the individual factors alone, was evaluated in a cohort of 26,961 adult patients receiving hernia repair. They exclusively evaluated perioperative respiratory events and found an incidence of 3.1% and a risk rate of 2.4 (95% CI: 1.8-3.2). These outcomes were even higher among overweight smokers below the age of 40 years; 8.0% and a risk rate of 6.3 (4.3-9.2). For comparison, the incidence of respiratory events was only 1.3% among those without smoking and overweight. Another recent cohort study with 55,240 patients evaluated the surgical site infection rate after hernia repair. Here, they found a dose-response with increasing rates at increasing BMI cut-of levels among smokers. BMI (OR 1.04; 95% CI 1.03–1.04;  $p < 0.001$ ) and smoking (1.51; 1.37–1.67;  $p < 0.001$ ) were the two most modifiable risk factors independently associated with this complication. Interestingly, the incidence was only 2% among non-smokers with BMI < 24.2, and 12% for smokers with BMI > 42.3. It would be clinically relevant to evaluate if an 'opposite' dose-response could be identified also during intervention for SNAP factors by the STRONG program. This objective is included in the present STRONG project.

Risky lifestyle plays a further role for recurrence of ventral hernia. A recent systematic review identified smoking (OR 1.34; 1.03-1.74) and BMI above 25 (2.51; 1.37-4.60) as preventable predictors for hernia recurrence as well as complications at the primary repair. Reduction of postoperative complications via successful prehabilitation would further add to the potential for recurrence reduction. However, alcohol and malnutrition were not included in those analyses.

Vi have identified only one study on co-existing SNAP factors performed by Liang and co-workers, who have reported a trend towards less wound complications of an up to six months program with physical exercise + weight reducing intervention: 7% versus 18%,  $p=0.1$ . At 2-year follow-up, there was no effect regarding complication- and recurrence-free patients, 73% versus 66%,  $p=0.4$ .

### **2c) STRONG-Hernia is powered for evaluation for postoperative complications**

A prior step towards the present STRONG-Hernia project has been taken by the ongoing STRONG – Cancer project, in which we are evaluating the effect of the STRONG program on lifestyle improvement and related risk reduction, exclusively from improvement of SNAP factors. STRONG-Cancer is an RCT recruiting a smaller group of patients scheduled for urothelial cancer surgery after preoperative neoadjuvant therapy. In a nested interview study, we collect the preferences among the recruited patients, their relatives, and staff (www.clintrials.gov NCT04088968; the Danish Scientific Ethical Committee H-20081571; the Danish Data Protection Agency P-2020-95). That trial does not aim at and therefore is not powered for evaluation on postoperative complications, health, and cost-effectiveness, like the present STRONG-Hernia project.

However, the positive process is useful for the present project on ventral hernia repair. Thus, the present project on ventral hernia repair is not a repetition of another project but adds completely new and clinically important knowledge to the research area of prehabilitation regarding SNAP factors.

## 3. Methods

### 3a. Designs, framework, analyses, randomisation, and control group

#### Design

The project uses multiple designs to test the hypotheses and answer the research questions presented in Chapter 2a, including a randomised design with nested qualitative, costs, and secondary cohort analyses, see figure 1.

Figure 1. Trial profile for STRONG-Hernia; CG= Control group, EXCL: Exclusion, FU: Follow-up, IG: Intervention group, OP: Operation, R: Randomisation, SNAP: Smoking, Nutrition (malnutrition and/or obesity), Alcohol, Physical activity.

[figure not shown]

#### Theoretical framework

Intervention targeting reduction of risk for postoperative complications is closely related to the preoperative recovery of dysfunctional organ systems prior to surgery, see figure 2.

Figure 2. Framework: Functionality and organ functions in the perioperative period. (OP: Operation. TAU: Treatment as usual)

[figure not shown]

Our intensive SNAP intervention is tailored to meet the individual patient's need for risk reduction at surgery via the intensive 6-week STRONG program including from one to five co-existing risky SNAP factors per session. The patients in the intervention group is introduced to the STRONG program as previously described in the World Health Organization publication 'Engage in the process of change' and elsewhere.

### Analyses

Analyses are done blinded as Intention-to-Treat (ITT). We will use Fisher's exact test for frequencies, Mann-Whitney for continuant variables, and  $p < 0.05$  is chosen for statistical significance. To benefit future meta-analyses, we will also give the parametric results. This would also meet the tradition that costs are usually reported with means and standard error (SE), mean difference (MD), and 95% confidence interval (CI). Bootstrapping procedures are used to calculate the cost-effectiveness plane and the acceptability curve by repeatedly resampling the data (1,000 incremental cost and effect pairs). Sensitivity analyses will be performed for differences in local standards for the control groups among the surgical centres. Analyses as per-protocol, dose-response, prediction, sensitivity, and the other secondary analyses are done by logistic regression models including control for confounders and effect-modifiers and reported as Risk Rates with 95% Confidence Interval (CI). The results are considered significant if the CI does not involve 1.00.

Absolute (ARR) is calculated as the events in the control group minus the events in the intervention group, and the relative risk reduction as the ARR divided by the events in the control group. The number needed to treat was calculated by  $1/ARR$ . We will present the mortality as Kaplan-Meier plots and test by the log rank test.

In case of dropouts, the primary outcome is collected from the medical record and a telephone follow-up after acceptance from the patient. In case of missing health data, the lifestyle at baseline will be imputed as the results in order not to over-estimate the results of changing lifestyle. This would expectantly impact the results to a similar degree in both groups.

All quantitative analyses are performed in SPSS Statistics® version 22.

The qualitative analyses are done using Kirsti Malterud's approach of systematic text condensation.

After import into NVivo® qualitative data analysis software version 11, the systematic text condensation in the four steps takes place: 1) Total impression of all answers and identifying preliminary themes, 2) coding by identifying and sorting meaning units, 3) condensation into code groups, and 4) synthesising the condensates into a story grounded in the empirical data.

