### Outcomes and data collection (Table 1)

Postoperative complications (within 1, 3, 6 months after surgery): The primary outcome is the number of patients with > 1 complication, defined by requiring documented treatment, categorized in accordance with the Clavien-Dindo grading and the Comprehensive Complication Index (CCI). They include adverse events and side effects. Secondly, length of stay, second surgery, revisits and – admissions at hospital, visits in primary care, time back to work or previous activities.

Successful risk reduction at follow-up/at surgery: Defined as SNAP below risk level validated as described in chapter 2; for obesity BMI < 30 or at least 5% and max 10% loss of body fat mass preoperatively (0.5–1 kg/weekly without developing malnutrition). Data are collected via logbook and validation.

For frailty: In addition to pI-protein, the frailty level (0-5, 0 is best) is measured by Fried's Modified Frailty Score according to Blammers as that is associated with development of complications. It includes five criteria:

- Slowness: Performance time in the walking test,
- Weakness: Hand grip strength measured by a dynamometer,
- Exhaustion: Responding "All the time" or "Often" to the item "I feel everything is an effort / I can't get going" in the Hospital Anxiety & Depression Scale.
- Weight loss: Self-reported 5 kg over the last year
- Low activity: Below 3 MET

Health (at baseline, after 6 weeks/at surgery, and 6 months postoperatively): This is measured by the health-related quality of life measured by EQ-5D with 5 dimensions and the overall health measured with a scale from 0 to 100 with a higher score representing a better health. Within 2 years of follow-up, the morbidity is measured as visits and stay at hospital as well as visits in primary care and prescribed medicine and grouped diagnoses groups as well as mortality.

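### Logistic regression and a CI-excludes-1.00 rule are fixed for a secondary tier that includes continuous and count health outcomes, for which no cut-off is given

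*Protocol*

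**What the plan says.** Protocol section 3a (Analyses) sets up two tiers.

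- **Intention-to-treat comparisons between arms.** "We will use Fisher's exact test for frequencies, Mann-Whitney for continuant variables". It adds: "To benefit future meta-analyses, we will also give the parametric results". Costs have means, mean differences and bootstrapping. Mortality has Kaplan-Meier plots and the log-rank test.
- **Everything else.** "Analyses as per-protocol, dose-response, prediction, sensitivity, and the other secondary analyses are done by logistic regression models". These models adjust for confounders and effect-modifiers and report risk rates with 95% intervals. The decision rule is: "The results are considered significant if the CI does not involve 1.00". No other regression model is named.

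Section 2a lists study 5B in the second tier: "Dose-response of SNAP factor improvement (number/type) and health on long-term as well as predictors for improved health". The hypotheses in the same section repeat it as a dose-response with health gain.

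The section on outcomes and data collection (Table 1) defines health. "This is measured by the health-related quality of life measured by EQ-5D", together with "the overall health measured with a scale from 0 to 100 with a higher score representing a better health". Over 2 years it adds hospital visits and stays, primary-care visits, prescribed medicine, diagnosis groups and mortality. The same section scores frailty from 0 to 5 and grades complications by Clavien-Dindo and by the Comprehensive Complication Index (CCI).

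**The concern.** The second-tier sentence fixes three things together: the model, the effect scale and the significance rule. All three belong to a yes/no outcome. Study 5B has health as its outcome, and most of the measures that define health are scores, counts or durations.

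Followed literally, the sentence means that EQ-5D, the 0-100 scale, visits and stays must each be turned into a yes/no variable before the model can be fitted, at a point the protocol does not give. Three things are at stake:

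- Information is lost in a pre-stated hypothesis.
- The result depends on a threshold that this document leaves open.
- If a per-protocol or sensitivity analysis of a continuous outcome is run under this rule, it estimates a ratio on a cut variable, while the intention-to-treat analysis of the same outcome is a rank test with a mean difference. If the two disagree, the reader cannot tell whether the population, the adjustment or the cut is the cause.

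**Working it through.** **1. The plan's own figure.** Section 4 (Power calculation) gives 2 x 199 for complication rates of 20% and 10%, 80% power and two-sided alpha 0.05. With the pooled-variance formula and mean rate 0.15:

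n = [1.960 x sqrt(2 x 0.15 x 0.85) + 0.842 x sqrt(0.20 x 0.80 + 0.10 x 0.90)]² / 0.10² = 199 per arm.

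Power is 80.0% at 199 and 80.2% at 200 per arm. The figure reproduces. It concerns a binary outcome, so this point does not touch it.

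**2. Which outcomes fit the second-tier rule.**

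| Outcome | Scale in the protocol | Fits binary logistic regression as written? |
|---|---|---|
| Complications; complication-free repair | yes/no | Yes |
| SNAP success | yes/no, with stated thresholds | Yes |
| Death within 2 years | yes/no, with its own methods | Yes |
| Frailty | ordered, 0 to 5 | Only if cut; ordinal logistic regression would fit and is not excluded |
| Clavien-Dindo grade | ordered grades | As for frailty |
| EQ-5D, 0-100 health scale | scores | Only if cut; no cut-off given |
| CCI | index, called a continuous scale in the title of its reference | Only if cut; no cut-off given |
| Visits, stays | counts, durations | Only if cut; no cut-off given |

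Where the protocol wants a yes/no outcome it can define one: for obesity, SNAP success is BMI below 30 or a loss of 5% to 10% of fat mass. Improved health has no such definition.

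**3. The 1.00 rule.** It is right for a ratio, whose null value is 1. A difference in means has null value 0. An interval for a mean difference can lie wholly above 0 and still contain 1.00, so the rule would give the wrong answer. As written, it leaves no room for a linear model.

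**4. Size of the loss, as an illustration.** Assumptions: the outcome is normal and the effect is small. The protocol gives no cut-point, so a range is shown. With a share p of patients on one side of the cut, the information kept relative to the uncut outcome is φ(z_p)² / [p(1 − p)], where φ is the standard normal density. For a median split this is 0.3989² / 0.25 = 0.637.

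Power is shown for a two-arm comparison with 200 per arm. A standardised difference of (1.960 + 0.842) x sqrt(2/200) = 0.280 has 80% power uncut.

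| Split | Information kept | Lost | 400 patients act like | Power (80% uncut) |
|---|---|---|---|---|
| 50/50 | 0.637 | 36% | 255 | 61% |
| 30/70 | 0.576 | 42% | 230 | 56% |
| 20/80 | 0.490 | 51% | 196 | 50% |
| 10/90 | 0.342 | 66% | 137 | 37% |

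The formula does not transfer directly to a 0-5 score, to CCI or to visit counts, which are discrete or likely to be skewed.

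**The case against.** Much can be said on the other side, and a good part of it stands.

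- **Randomised comparisons.** A reader might infer that all the non-binary secondary outcomes are to be cut. The text does not support this. The intention-to-treat comparisons use Mann-Whitney with parametric results added, so they stay on the full scale. This stands.
- **Dichotomising is never mentioned.** The protocol speaks of logistic regression models in general, and ordinal logistic regression is one of them. For frailty and Clavien-Dindo grade a cut is therefore not forced. This stands for ordered categories. It is a much less natural reading for EQ-5D, a 0-100 score, CCI or visit counts.
- **Mortality.** Death by 2 years is binary and already has Kaplan-Meier and log-rank, so it does not belong on the list. This stands.
- **Robustness analyses.** The one sensitivity analysis described concerns local control-group standards and names no continuous outcome. For the binary primary outcome, logistic per-protocol and sensitivity analyses are suitable. It would be wrong to say that they cannot check the trial's main result.
- **Study 5B as a responder analysis.** Predictors of improved health could be predictors of a yes/no response, with the threshold left to an SAP that is not at hand. That is possible, and a threshold absent from the protocol is no evidence that it will be chosen after the data are seen. But the dose-response part of 5B has health itself as its outcome, and the model, the ratio scale and the 1.00 rule are stated here rather than left open. An SAP that used a linear model would depart from the protocol.
- **Power.** Section 4 claims power for complications and coverage of lifestyle improvements and costs, not for long-term health. So the loss is of information, not of a promised power. This stands.

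**Conclusion.** The point holds in a limited form. The second-tier rule suits its binary targets. It does not suit the continuous and count measures that define health in study 5B, nor any adjusted, per-protocol or sensitivity analysis of such measures or of CCI. For these, binary logistic regression needs a cut-off that the protocol does not give, and the 1.00 rule is wrong for a difference. This is a stated rule that fits badly, not merely a missing detail.

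A reader might take a loss of a third to a half as a property of this trial. It is not. The range of 36% to 51% holds only for a normal outcome split between 50/50 and 20/80; a 10/90 split loses 66%, and the figures for discrete or skewed scores would differ.

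The primary outcome, the 199 per arm and the intention-to-treat comparisons stand as they are. The correction is still worth making because 5B is a stated hypothesis and the change is cheap.

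**What to change.** Reword the second-tier sentences in section 3a (Analyses):

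- Limit binary logistic regression to binary outcomes: complications, complication-free repair and SNAP success.
- Use linear regression with robust or bootstrap confidence intervals for EQ-5D, the 0-100 health scale and CCI, and state the null value for differences as 0.
- Use ordinal logistic regression for frailty and Clavien-Dindo grade.
- Use a count model, such as negative binomial regression, for visits and stays.
- Keep 1.00 as the null value for ratio measures only.
- If a responder definition of improved health is wanted, fix and justify its threshold before the data are analysed.

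The cost is one paragraph of wording and no new data. The drawback is that the secondary results will carry several effect measures instead of one.
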